## Abstract

**Background:**

Feeding intolerance is a common problem in preterm infants, which is associated with an increased risk of infections, prolonged hospitalization, and increased economic costs. When human milk is not available, formula feeding is required. Amino acid-based formula and extensively hydrolyzed formula could be considered for use for severe feeding intolerance. A recent Cochrane meta-analysis found that preterm infants fed extensively hydrolyzed formula compared with standard formula could not reduce the risk of feeding intolerance and necrotizing enterocolitis, and weight gain was slower. Some studies reported that preterm infants fed amino acid-based formula could reduce the gastric residual volume. We hypothesize that amino acid-based formula can improve feeding intolerance and establish full enteral feeding more rapidly in preterm infants compared with extensively hydrolyzed formula.

**Method:**

The randomized, prospective, controlled trial was conducted at the Children's Hospital of Chongqing Medical University (Chongqing, China). A total of 190 preterm infants with gestational age <32 weeks or birth weight <1,500 g and with a diagnosis of feeding intolerance were included. Patients were randomized to an amino acid-based formula-fed group and an extensively hydrolyzed formula-fed group. The primary outcome is the time (days) to reach full enteral feedings. Secondary outcomes include duration of vomiting and abdominal distension, gastric residual volume, body weight, length and head circumference during hospitalization, length of hospital stay (days), cost of hospitalization, time (days) of parenteral nutrition, change of abdomen circumference, main serum parameters, and incidence of adverse events.

**Discussion:**

The successful implementation of our study will provide robust evidence for formula alternatives in preterm infants with feeding intolerance.

**Clinical Trial Registration:**

www.ClinicalTrials.gov, identifier: NCT05347706.

## Background

Globally, approximately 15 million premature infants are born every year, with this number increasing progressively (1). Due to the immature digestive, absorptive, and immunologic functions, preterm infants are particularly susceptible to mucosal inflammation and bacterial overgrowth, which can lead to feeding intolerance (FI) (2). FI frequently occurs in premature infants, especially in those with a gestational age of <32 weeks or a birth weight of <1,500 g (3, 4). FI is defined as the inability to digest enteral feeding and is characterized by increased gastric residuals, abdominal distension, vomiting, or both (5). This delays the establishment of full enteral nutrition and extends the duration of parenteral nutrition, thus increasing the risk of infections, prolonging the length of hospital stay, and increasing economic costs (6).

At present, there are some prevention and treatment measures for FI including optimization of enteral nutrition, modification of feeding methods, use of probiotics or medicine, and nursing interventions, but these measures are not fully effective (7, 8). The feeding strategy for FI is an important clinical challenge for neonatologists. Associated with less feeding intolerance, human milk (HM) is recommended by the World Health Organization (WHO) as the first-choice milk for preterm. However, HM is not always available because of the lack of breast milk banks, diseases of the mother, and geographic factors, and therefore, formula feeding is required.

Currently, the alternative formulas include Preterm Formula (PF), Partially Hydrolyzed Formula (PHF), Extensively Hydrolyzed Formula (EHF), Amino Acid-Based Formula (AAF), etc. PF is used in preterm infants when human milk is not available (9). Clinically, PHF, EHF, and AAF are commonly used in treatment for moderate to severe cow's milk protein allergy and prevention for patients at high risk for allergy (10, 11). PF containing intact protein may not be appropriate for infants with FI (12, 13). Recently, a guideline mentioned that PHF, EHF, and AAF could be considered for use in severe feeding intolerance (8).

Mihatsch et al. (14) reported that EHF improved the feeding tolerance and enabled a more rapid establishment of full enteral feeding compared with standard PF in preterm infants. The use of EHF could reduce acid gastro-esophageal reflux in preterm infants with FI (13). A recent Cochrane meta-analysis found that existing data did not support conclusions that feeding PHF or EHF affected the risk of FI or necrotizing enterocolitis (NEC), but the data that could be abstracted from published studies for analysis were limited (3). Raimondi et al. (15) reported that preterm infants with severe feeding intolerance significantly and rapidly reduced the gastric residual volume after AAF introduction. Jang et al. (16) found the fecal calprotectin levels in AAF-fed infants with FI were significantly lower than those in the HM- or PF-fed infants with FI and showed improvement in the symptoms and signs of FI. However, these studies have some defects, such as small sample sizes and no randomization. Which formula is more suitable for preterm infants with FI? No scientific evidence is available at present.

Based on previous research, we design a randomized, prospective, clinical trial of AAF vs. EHF in feeding intolerance. We hypothesize that AAF can improve feeding intolerance and establish full enteral feeding more rapidly compared with EHF.

### Aim

The aim of the present study is to investigate whether AAF enables a more rapid establishment of full enteral feeding in preterm infants with FI compared with EHF and help establish improved guidelines and feeding practices.

## Method/Design

### Study Design

This study is designed as a single*-*center, randomized, prospective, blinded clinical trial. A total of 190 preterm infants with gestational age <32 weeks or birth weight <1,500 g with a diagnosis of FI were included in the study. They were randomized to the AAF group or the EHF group. Figure 1 shows the overall design of the study. Table 1 shows the data collection schedule.

**Figure 1 F1:**
[figure not shown]
The overall design of the study.

**Table 1 T1:** Data collection schedule.

	**Staff member**	**T1**	**T2**	**T3**	**T4**	**T5**
Symptom of FI	Neonatal physician	**×**				
Informed consent	Research assistant	**×**				
Contact information	Research assistant	**×**				
Sex	Neonatal physician		**×**			
Gestational age	Neonatal physician		**×**			
Mode of delivery	Neonatal physician		**×**			
Apgar score	Neonatal physician		**×**			
Maternal issues	Neonatal physician		**×**			
Weight	Neonatal nurse		**×**			**×**
Gastric residual volume	Neonatal nurse			**×**	**×**	
Abdominal circumference	Neonatal nurse			**×**	**×**	
Length	Neonatal nurse		**×**			**×**
Head circumference	Neonatal nurse		**×**			**×**
Time to reach total enteral nutrition	Neonatal physician					**×**
Duration of abdominal distension	Neonatal physician					**×**
Duration of vomiting	Neonatal physician					**×**
Length of hospital stay	Neonatal physician					**×**
Cost of hospitalization						**×**
Time of parenteral nutrition	Neonatal physician					**×**
Main serum parameters	Neonatal physician			**×**	**×**	
Incidence of adverse events	Neonatal physician					**×**

*T1 screening; T2 baseline evaluation; T3 beginning of intervention; T4 end of intervention; T5 discharge*.

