### Feeding Schedule

According to the guideline for nutrition support (19), enteral feeding is started within the first 24 h of life. Human milk is encouraged, and preterm formula is fed when human milk is not available due to the mother's or family's condition. Patients with FI are temporarily fed with AAF (Neocate® Nutricia, London, UK) or EHF (Alfare® Nestle, Netherlands) instead of HM or PF. Nutritional feeds start at 15–20 mL/kg/day and are increased by 20–30 mL/kg/day. The gastric residual volume (GRV) is checked before each feeding. If GRV is ≥ 50% of the previous feeding, then enteral feeding was ceased for 1 h, and patients are reassessed. If GRV is not improved, complete blood count, C-reactive protein (CRP), and abdominal X-rays are performed and assessed. If these results can rule out NEC and severe infection, patients are fed in the same amounts for 2–3 days. Enteral feeding is increased at the same rate until full enteral feeding (150 mL/kg/day) every 3 h is reached. Enteral feedings are withheld: in the presence of bloody or biliary gastric residuals, in cases of abnormal abdominal examination, and/or in cases of abnormal abdominal X-ray. As soon as the residuals, the abdominal examination, and/or X-ray return to normal, feeding is resumed with AAF or EHF at the same speed. Once the patients with FI show clinical improvement, AAF or EHF feeding is discontinued, and the previous feeding, either HM or PF is resumed. When full enteral nutrition is insufficient, all patients receive parenteral nutrition solutions (6), which are gradually decreased with increasing enteral feeding. Other routine treatments for FI are given in the two groups according to the guidelines. Table 3 shows the study formulas. Figure 2 shows the feeding schedule.

**Table 3 T3:** Study formulas.

**Characteristics**	**Study formula**	
	**AAF**	**EHF**
Nutrient density (KJ/100ml)	279	284
Nutrient composition per 100 ml		
Total Protein (g, % calories)	2.0,12%	1.82,11%
Total Carbohydrate (g, % calories)	7.0,42%	7.5,43%
Total Fat (g, % calories)	3.4,46%	3.39,46%
Arachidonic acid (ARA), mg	11.3	8.5
Docosahexaenoic acid (DHA), mg	11.3	8.5
Minerals		
Phosphate (mg/100 ml)	59	46
Calcium (mg/100 ml)	85	68
Iron (mg/100 ml)	1.1	0.7
Osmolarity (mOsm/L)	310	170

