#### Secondary Outcome

Duration of vomiting and abdominal distension (a 24-h abdominal circumference increase of ≥1.5 cm).Gastric residual volume (measured by aspirating with a 5-ml syringe before each feeding).Body weight, length, and head circumference during hospitalization.Length of hospital stay (days).Cost of hospitalization.Time (days) of parenteral nutrition.Change of abdomen circumference (measured at a specific time every day).Main serum parameters (blood, liver and kidney function, and electrolytes).Incidence of adverse events.

**Study endpoint**: The day of discharge

**Follow*-*up plan**: No.

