## Discussion

This randomized, prospective, clinical trial aims to assess the effects of AAF or EHF on improving FI. A total of 190 preterm infants with FI are included and randomly divided into two groups: the AAF-fed and EHF-fed groups. Time to reach full enteral feedings, duration of vomiting, abdominal distension and gastric residual volume, and other indicators are evaluated.

The mechanisms by which AAF improves feeding intolerance remain incompletely unclear. AAF is composed of free amino acids, no lactose, and a higher percentage of medium chain triglycerides. The amino acids are essential for intestinal function and have an important role in mucosal blood perfusion, growth, and immunity (20). AAF may promote gastric emptying, decrease the duration of parenteral nutrition, and reduce the risk of nosocomial infections and parenteral nutrition-associated complications.

However, there have been some concerns as to whether AAF and EHF meet the nutritional needs of preterm infants (16, 21). In this study, the patients with FI are fed AAF or EHF for a short term; once the clinical presentation of FI improved, HM or PF are switched back. Jang et al. (16) reported that the patients with FI who fed AAF for a short term showed improvement in the symptoms and signs of FI with proper body weight gain, and did not develop any adverse clinical signs or symptoms during AAF feeding. There was not any disadvantage in preterm infants on growth between the EHF-fed group and the PF-fed group in the long-term (12 weeks) study (22), and long-term treatment with AAF was safe and allowed adequate body growth (23).

The study also has some limitations that should be noted. Due to the imperfect follow-up system, the lack of post-intervention follow*-*up makes it difficult to judge long*-*term prognosis. Additionally, the study population are low birth weight preterm infants with a high risk for FI, who are not representative of the entire neonatal population, and therefore, the findings may not be generalizable to other populations. Furthermore, the study formulas differ not only in the protein equivalent component (free amino acids vs. extensively hydrolyzed protein), but also in other aspects (such as nutrient density, osmolarity, and minerals). These differences may potentially contribute to the differences in results. The study design does not permit us to elaborate on the different effects of each of these differences separately.

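### Table 1 schedules several secondary outcomes only at end of intervention or at discharge, times that depend on how the infant responds, and for residuals and abdominal circumference it contradicts the outcome list

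*Protocol article*

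**What the plan says.** The footnote to Table 1 (data collection schedule) defines the time points: "T1 screening; T2 baseline evaluation; T3 beginning of intervention; T4 end of intervention; T5 discharge". Within that table:

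- gastric residual volume, abdominal circumference and main serum parameters are marked at T3 and T4 only;
- weight, length and head circumference are marked at T2 and T5 only.

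The Feeding Schedule section says what ends the intervention: "Once the patients with FI show clinical improvement, AAF or EHF feeding is discontinued, and the previous feeding, either HM or PF is resumed". The Discussion repeats it: "once the clinical presentation of FI improved, HM or PF are switched back". Neither gives a fixed duration or a numerical threshold.

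The Secondary Outcome section lists length of hospital stay as an outcome, sets the day of discharge as the study endpoint and plans no follow-up.

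The text describes more frequent measurement than Table 1. Feeding Schedule: "The gastric residual volume (GRV) is checked before each feeding". Secondary Outcome, on the abdomen: "Change of abdomen circumference (measured at a specific time every day"; on growth: "Body weight, length, and head circumference during hospitalization".

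The Statistical Analyses section compares continuous outcomes by t-test or Mann-Whitney U test. It names no time point and no adjustment for elapsed time.

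**The concern.** An end-of-intervention visit that is usually triggered by improvement catches infants when they have reached a similar clinical state, however long that took. If one formula works faster, the difference lies in the time taken to reach T4, and little of it remains in the values recorded there. This applies most directly to residuals and abdominal circumference, which are themselves signs of feeding intolerance. Serum values at T4 follow exposures of unequal length at unequal ages, so a difference or its absence is hard to attribute to the formula.

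Growth has the opposite problem. If one arm stays in hospital longer, its infants have had more days to grow by T5, so raw discharge weight, length and head circumference tend to favour the slower arm. The Discussion itself notes doubts about whether these formulas meet the nutritional needs of preterm infants, so a distorted growth comparison matters for interpretation.

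**Working it through.** **1. The plan's own figures.** The article gives no figure for assessment times. The nearest is the design difference in the Sample Size section, 0.30 × 23.6 = 7.08 days. With SD 15.6, n = (1.96 + 0.84)² × 2 × 15.6² / 7.08² = 76.13 per group, and 76 / 0.8 = 95 per group, 190 in total. The stated sample size reproduces, and this point does not depend on it.

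**2. The passages side by side.**

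| Outcome | Table 1 | Text | Reading |
|---|---|---|---|
| Gastric residual volume | T3, T4 | Before each feed (Feeding Schedule, Secondary Outcome) | Contradiction; compared time not stated |
| Abdominal circumference | T3, T4 | Daily (Secondary Outcome) | Contradiction; compared time not stated |
| Serum parameters | T3, T4 | No time given | T4 is the only post-baseline time |
| Weight, length, head circumference | T2, T5 | During the hospital stay, no day fixed | T5 is the only scheduled post-baseline time |

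T2 and T3 do not depend on response to the formula. T4 and T5 do.

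**3. Illustration of a response-triggered comparison.** All inputs are assumed except the 95 per arm. The residual, as a percentage of the feed, starts at 60% and decays exponentially. Each infant has its own time constant, with a median of 5 days in one arm and 5 × 1.3 = 6.5 days in the other, and measurement noise has SD 6 points. Every infant stops at its first daily value below 15%, 20% or 30%. Each setting was simulated 1,000 times and compared by t-test at 5%.

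| Time of comparison | Mean arm difference (points) | Share of tests significant |
|---|---|---|
| T4, triggered by improvement | about 0.3 to 0.6 | about 9 to 15% |
| Fixed day 3, 5 or 7 | about 4.6 to 5.2 | about 83 to 88% |

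The mean stopping day differed between arms by about 1.0 to 1.9 days. The effect was present, but the triggered visit removed most of it from the measured value. The model contains no exits for other reasons, so it shows the mechanism and does not predict this trial.

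**4. Growth at discharge.** Shift in discharge weight = gain per day × difference in stay. Both inputs are assumed.

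| Gain (g/day) | Stay differs by 3.5 days | Stay differs by 7 days |
|---|---|---|
| 15 | 52.5 g | 105 g |
| 20 | 70 g | 140 g |
| 30 | 105 g | 210 g |

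Elapsed time alone would therefore move discharge weight by about 53 to 210 g. The 7-day end of the range is close to the 7.08-day design difference, but that figure concerns time to full enteral feeding. The article does not link it to length of stay.

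**The case against.** The strongest reply is that the article never says residuals and circumference are compared at T4. A reader might infer it from Table 1, but the Statistical Analyses section names no time point, and the text describes per-feed and daily measurement, so fixed-day data should exist. An analysis plan that is not shown may set the comparison time. This stands. For these two outcomes the supported finding is a contradiction over what is recorded, together with the bias that would follow if Table 1 governed. An analysis plan would not settle that contradiction, because it can use only what the schedule collects.

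Other tempting readings also go too far:

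- *Every infant is measured after doing well.* The Exit Criteria include death, discharge before total enteral nutrition, withdrawal, sepsis, NEC, ventilatory support and critical illness. Some infants stop the formula without improving.
- *Residuals are analysed in millilitres.* The outcome list mentions a 5-ml syringe but gives no analysis unit. The inclusion criteria and the Feeding Schedule judge residuals against the previous feed.
- *Raw discharge weight is the planned comparison.* The outcome list refers to the whole stay, and the T2 and T5 values with length of stay already allow a growth rate to be calculated.
- *The abstract warns of slower growth in one of these two arms.* Its remark compares extensively hydrolyzed with standard formula, not the two study formulas with each other.

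For serum values, a before-and-after pair around the exposure is a defensible tolerability measurement. The difficulty lies in reading it as a comparison of arms when exposure lengths differ.

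**Conclusion.** The point holds in a limited form. T4 generally follows clinical improvement and T5 is discharge, so comparisons made there with unadjusted tests do not compare the arms at like times. This applies most firmly to serum parameters and to growth, for which Table 1 gives no other post-baseline time. For residuals and abdominal circumference, Table 1 contradicts the text, and the bias towards no difference arises only if the Table 1 schedule is the one analysed.

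The sizes rest on assumptions. The 53 to 210 g shift needs a 3.5 to 7 day difference in stay and a gain of 15 to 30 g/day. The loss of signal at T4 needs the recovery model set out above.

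Only secondary outcomes are affected. The primary outcome is the age on the first day of sustained full enteral feeding, which is not a value read at T4 or T5, and the sample size is unaffected. A reader might infer that the trial's main result is compromised; nothing in the article supports that.

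**What to change.** 1. Reconcile Table 1 with the Feeding Schedule and Secondary Outcome sections, so that the residual and circumference values already being measured are entered daily.
2. Compare the arms on these two outcomes at fixed days from randomisation (for example daily to day 7, in a repeated-measures model), adjusted for the T3 value. Keep infants in the comparison after they return to human milk or preterm formula. Express residuals as a percentage of the previous feed, the scale the protocol already uses for its criteria.
3. Analyse growth from T2 to T5 as g/kg/day or as change in z-score for postmenstrual age, adjusted for baseline, and not as raw discharge values.
4. Report T4 serum values as descriptive, alongside duration of exposure to the study formula.

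The cost is some extra data entry and analysis work and a revised Table 1. No new measurement of the infants is needed.

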### Study Setting

All subjects were recruited in the Children's Hospital of Chongqing Medical University (Chongqing, China), a tertiary university hospital that has a 250-bed neonatal unit with an annual admission rate of around 8,000 neonates in the past 2 years.

### Study Population

Table 2 specifies all inclusion and exclusion criteria.

**Table 2 T2:** Inclusion and exclusion criteria.

Inclusion criteria
• Admission between December 2021 and December 2023.
• Gestational age (GA) <32 weeks or birth weight (BW) <1,500 g, appropriate for gestational age, admitted to Department of neonatology, Children's Hospital of Chongqing Medical University within the first 24 h after birth, maximal enteral intake <50 ml/kg/day
• Patients are fed with PF when HM is not available after admission
• Meet the diagnostic criteria of FI. Currently, a clear and universal definition of FI is lacking, FI is defined as follows with reference to relevant literature (5, 16–18): One or two of the criteria below are met: (1) gastric residual volume ≥50% of the previous feeding volume (≥ two times within 24 h), with the presentation of vomiting and/or abdominal distension; (2) feeding plans fail: including feeding withheld or decrease > 6 h, or not increased >24 h (5)
• Parental consent has been obtained
Exclusion criteria
• Perinatal asphyxia: (1) Apgar score of <4 at 5 min; (2) Fetal umbilical artery acidemia: pH <7.00 and/or base deficit worse than or equal to minus 12 mmol/L; (3) A significant peripartum or intrapartum hypoxic-ischemic event (e.g., uterine rupture, placental abruption, cord prolapse, amniotic fluid embolism, fetal exsanguination from a vasa previa or massive feto-maternal hemorrhage, etc.).
• Potential metabolic or chronic disease, congenital abnormality, or any other diseases that may affect feeding ability, normal growth, and development before recruitment
• Patients who need surgical treatment under general anesthesia (ligation of patent ductus arteriosus is excluded) before or on the date of randomization
• Blood pressure is unstable (allowing for dopamine <5 μg/kg/min)
• Ventilator dependence or FiO2 >40% on the date of randomization (allowing for nasal intubation, CPAP, and/ or oxygen mask)
• Grade III or IV intraventricular hemorrhage is diagnosed before or on the date of randomization

